### Data management {19}

Data archiving takes place in a PAIN2.0 database that holds all documentation. The principle of data management and data protection has been described in a comprehensive data management plan.

### Confidentiality {27}

The following patient data are collected and processed in the centres:Administrative data (e.g. name, date of birth, health insurance company, and the name of the responsible study doctor) only remain in the centres and are used for medical care according to the study conditions and for the organisation of follow-up interviews and group procedures. These data must be retained for a period of 10 years. The list remains at the centre and is the only link between pseudonymised patient ID and the health insurance data.All other information on patient care and evaluation is entered into the PAIN2.0 database exclusively in pseudonymised form, following the written consent of the study participants. In the PAIN2.0 database, the pseudonymised patient data for each centre are presented in separate overviews, with data from other centres being inaccessible.

Questionnaire data for evaluation is entered into the PAIN2.0 database exclusively in pseudonymised form.

### Plans for collection, laboratory evaluation and storage of biological specimens for genetic or molecular analysis in this trial/future use {33}

N/a. There are no plans for collection, laboratory evaluation and storage of biological specimens for genetic or molecular analysis in the current trial and future use in ancillary studies.

### Statistical methods

#### Statistical methods for primary and secondary outcomes {20a}

The primary analysis model for the two primary outcomes (pain intensity and disability score at 6 months adjusted for baseline values) is a linear mixed regression model with a random intercept.

The values of the primary outcomes at time *t*_3_ (6-month follow-up) serve as the dependent variables. To describe the effect of the intervention, the baseline value at time t_0_ and group membership are used as predictor variables [38, 39]. As two primary endpoints are analysed simultaneously, adjustment for multiple testing using Bonferron’s method will be applied.

When using these models, it is possible to include further predictor variables in the analysis. This can be of interest if, despite randomisation, relevant differences occur between the study arms and must be statistically controlled, or if the effects of covariates (e.g. of age or other patient characteristics) are to be analysed. Through appropriate model specification, all hypotheses of interest can be tested with these analysis methods.

The analysis of the primary endpoints will be conducted according to the intention to treat (ITT) principle.

The primary and secondary outcomes to be investigated are predominantly continuous data for which linear regression models can be used. However, the family of (generalised) mixed models also allows analogous evaluations for other types (ordinal or categorical) of dependent variables.

In the context of the analysis of days of incapacity to work or cost data, it may furthermore be necessary to use special analysis methods for data with an asymmetric distribution or with heavily populated zero cells (‘zero-inflated’).

Statistical significance tests are performed with an α-level of 0.05 (two-sided). In the confirmatory analysis of the primary outcome measures, a Bonferroni adjustment for multiple testing (3 outcome measures, 2 follow-up times) is applied. No such adjustment is used in the exploratory analyses of the secondary outcomes.

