#### Trial design {8}

The study is designed as a nationwide, multicentre randomised controlled trial (RCT), with two parallel groups to evaluate the efficacy of a 10-week outpatient interdisciplinary multimodal pain therapy. The duration of study participation is 12 months. Patients are enrolled consecutively from January 2023 to February 2024. Following verification of inclusion and exclusion criteria, they will be allocated to either the intervention group or the control group in a 1:1 ratio. The intervention is scheduled to occur between March 2023 and November 2024. Control group patients will receive standard care for 6 months, with the option to participate in the intervention program subsequently. Please refer to Fig. 1 for an overview of the study’s procedural timeline.

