### Interventions

#### Explanation for the choice of comparators {6b}

The comparator is the standard healthcare as currently applied in the standard pain therapy in Germany. Patients in the intervention group will receive the new intervention at the beginning of the first 6 months, whereas participants in the control group will not receive any trial-related healthcare interventions. However, they are permitted to continue their pre-existing medical, physiotherapeutic and/or psychological (pain-related) therapies, which is often referred to as ‘treatment as usual’.

The comparator was chosen to identify the effects of the new intervention and to improve the currently applied pain therapy. Therefore, a comparison to ‘usual care’ is eligible. It is worth noting that patients in the control group also receive interventions after the initial 6 months (Fig. 2; see also Fig. 1).

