### Intervention description {11a}

Interdisciplinary multimodal pain therapy [15] is commonly applied in chronic pain treatment. It is described as an integrative therapy approach consisting of somatic, psychotherapeutic, and physiotherapeutic interventions. Physicians, physiotherapists and psychologists collaborate equally in an integrative team approach and regularly coordinate and align on diagnosis, treatment plan and treatment progress. The primary goal of treating chronic pain by IMPT is to restore the patient’s subjective and objective functioning and self-control.

In this project, the IMPT is applied to an outpatient setting (A-IMPT) and adapted to the aims for the above-described target population.

The A-IMPT takes place once a week for 3 h in 10 sessions over 12 weeks in groups of 10 patients. It consists of 5 modules in total, each thematically grouped (Fig. 3). There are two sessions within each module, led by the respective professions. Throughout the 10 sessions, psychologists and physiotherapists are each present for a total of 30 h, while the presence of the physicians in the group sums up to 15 h. It is important to note that the content within each module is taught collaboratively by one or more professions.

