### Assignment of interventions: allocation

#### Sequence generation {16a}

Lists of randomised blocks of varying lengths were generated by the evaluating institute for each participating centre and implemented in the PAIN2.0 database.

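### The primary model has one random intercept of unstated level and no therapy-group variance, although A-IMPT is given in groups of 10 in one arm during the primary window

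*Protocol article*

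**What the plan says.** **Model.** In the protocol article, Statistical methods for primary and secondary outcomes {20a}, the primary model "is a linear mixed regression model with a random intercept". The 6-month values of the two primary outcomes ("6-month follow-up) serve as the dependent variables") give one value per patient and outcome, and "the baseline value at time t_0_ and group membership are used as predictor variables". Group membership here means study arm. The level of the intercept is not named, and no term for therapy group appears.

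**Delivery.** Intervention description {11a}: "The A-IMPT takes place once a week for 3 h in 10 sessions over 12 weeks in groups of 10 patients".

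**Controls.** Explanation for the choice of comparators {6b}: "participants in the control group will not receive any trial-related healthcare interventions" during the first 6 months. Trial design {8}: "Control group patients will receive standard care for 6 months, with the option to participate in the intervention program subsequently".

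**Randomisation.** Patients are randomised individually. Sequence generation {16a}: "Lists of randomised blocks of varying lengths were generated by the evaluating institute for each participating centre".

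**Sample size.** Sample size {14} refers to a simplified multilevel model simulated in MLPowSim. It states a difference of 0.3, residual variance 1.0, 500 analysed and 782 randomised. It gives no levels, cluster size or ICC.

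**The concern.** Members of a therapy group share therapists, sessions and each other over ten meetings, so their 6-month scores may be correlated beyond what centre explains. Controls have no such grouping before the primary endpoint. Clustering of this kind, present in one arm only, adds variance to the treatment contrast.

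The single intercept can be read at three levels:

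- **Patient.** With one dependent value per patient, this variance cannot be separated from the residual.
- **Centre.** This is the natural reading, given the per-centre randomisation lists. The effect is common to both arms, so it largely cancels from the contrast and leaves the one-arm group variance unmodelled.
- **Therapy group.** The text does not exclude this. It would need a rule for ungrouped controls and would leave out centre, the randomisation stratum.

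No single intercept covers both centre and therapy group. If the centre reading is followed and group outcomes are correlated, the confidence intervals for both primary endpoints are too narrow and the confirmatory tests exceed their nominal level.

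**Working it through.** **Inputs from the article.** Groups of 10; 22 facilities; 782 randomised 1:1; 500 analysed, so 250 per arm; difference 0.3; residual variance 1.0; Bonferroni adjustment for two endpoints, so 0.05/2 = 0.025 each.

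**Assumed.** Therapy-group ICC of 0.02, 0.05 or 0.10; total variance equal in both arms; groups containing intervention-arm patients only.

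**Does the stated sample size reveal an allowance for clustering?** For independent data, n per arm = 2 × ((z₁₋α/₂ + z₀.₈₀)/0.3)².

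- α = 0.05: 2 × ((1.960 + 0.842)/0.3)² gives 175 per arm, 350 in total.
- α = 0.025: 2 × ((2.241 + 0.842)/0.3)² gives 212 per arm, 424 in total.
- α = 0.05/4: 496 in total.

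The stated 500 is 500/350 = 1.43 or 500/424 = 1.18 times the first two totals. The surplus could be a clustering allowance or a stricter alpha, and the article does not say which.

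**Cluster numbers.** 782/2/10 ≈ 39 groups, and 39/22 ≈ 1.8 groups per centre. Analysed patients per group: m = 10 × 500/782 ≈ 6.4. If only the stated 20% drop-out is applied, m = 10 × 0.8 = 8.

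**Formulas.**

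- Design effect in the intervention arm: DE = 1 + (m − 1) × ICC.
- True variance of the difference over modelled variance: v = (1 + DE)/2, because the control arm has DE = 1.
- True level of a nominal 0.025 test: 2 × (1 − Φ(2.241/√v)).

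| m | ICC | DE | v | SE ratio √v | True level |
|---|---|---|---|---|---|
| 6.4 | 0.02 | 1.11 | 1.05 | 1.03 | 0.029 |
| 6.4 | 0.05 | 1.27 | 1.13 | 1.07 | 0.035 |
| 6.4 | 0.10 | 1.54 | 1.27 | 1.13 | 0.047 |
| 8 | 0.02 | 1.14 | 1.07 | 1.03 | 0.030 |
| 8 | 0.05 | 1.35 | 1.175 | 1.08 | 0.039 |
| 8 | 0.10 | 1.70 | 1.35 | 1.16 | 0.054 |

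At ICC 0, v = 1 and the level is 0.025.

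**Does fitting centre repair this?** I simulated 22 centres and 39 intervention-arm groups of 6 or 7 (250 per arm), with an assumed between-centre variance of 0.05. The fitted model had centre effects (as fixed terms) but no group effect (200,000 runs). Rejection rates at nominal 0.025 were 0.025, 0.029, 0.037 and 0.048 for ICC 0, 0.02, 0.05 and 0.10. Adjusting for centre does not remove the inflation.

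**Mixed groups.** Controls may enter A-IMPT after 6 months, and nothing excludes groups that mix the two arms. With an illustrative 4 or 5 intervention-arm members per group and ICC 0.05, DE = 1.15 or 1.20 and the true level is 0.031 or 0.033.

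**The case against.** The strongest objection is that the article is condensed and the SAP is not shown. Naming random-effect levels and degrees-of-freedom methods is ordinary SAP content. A reader might infer from the article that group clustering is ignored and that the standard errors are too small. The text supports neither as fact: the intercept's level is unstated rather than stated to be centre, therapy group is not ruled out, and understatement also needs a positive ICC. That part of the objection stands. It does not remove the point, because the article does fix the random structure of the confirmatory model as one intercept, and one intercept does not fit the delivery it describes.

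The opposite inference, that the multilevel sample-size model and its surplus over 424 show that clustering was covered, is not supported either. No levels or ICC are given, and dividing 0.05 by four would explain the total almost as well.

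Further objections stand in part:

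- The size rests on an undocumented ICC. At 0.02 the effect is small.
- The figure of 8 per group does not match 500 analysed of 782. About 6.4 does.
- The 0.025 level follows the two-endpoint statement in {20a}. The same section also mentions 3 outcome measures at 2 follow-up times. At 0.05/6 = 0.0083 and 6.4 per group, the true levels would be 0.010, 0.013 and 0.019.
- With under two groups per centre, a separate group variance will be estimated imprecisely. That is a cost of the remedy and does not justify leaving the variance out.

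**Conclusion.** The point holds conditionally, and the model should be changed. The documents establish that therapy groups exist in one arm only during the primary window, that the model has a single intercept of unstated level, and that no therapy-group variance is specified. If the intercept is for centre, the standard error is understated whenever the therapy-group ICC is above zero.

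With 6.4 analysed patients per group, correct confidence intervals would be about 3%, 7% or 13% wider at an assumed ICC of 0.02, 0.05 or 0.10. The effect is minor at 0.02 and material from 0.05 upwards. It is smaller if therapy groups also contain control patients, and absent at ICC 0. These sizes rest on the assumed ICC, equal total variance in the two arms and the 0.025 level.

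**What to change.** Before the analysis, specify the primary model for each outcome as the 6-month value on baseline value and arm, with:

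- a random intercept for centre;
- a therapy-group random effect for intervention-arm patients only;
- controls, and intervention patients who never joined a group, entered as singletons, so that the intention-to-treat set stays intact;
- Kenward-Roger or Satterthwaite degrees of freedom.

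State also which levels and ICC the sample-size simulation assumed.

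**Cost.** A few sentences in the plan and a pseudonymised therapy-group identifier in the analysis file. The article does not say that the study database holds one. Confidentiality {27} keeps the administrative data used to organise groups at the centres, so the identifier may have to be requested from them.

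**Downside.** Confidence intervals widen slightly if the ICC is positive, and the group variance may be estimated at zero. With 250 per arm, a difference of 0.3 and 6.4 per group, power at 0.025 is Φ(0.3/√((1 + DE)/250) − 2.241). That is 86.7% at ICC 0 and about 85%, 82% and 77% at ICC 0.02, 0.05 and 0.10.

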**Methods:**

PAIN2.0 is designed as a multicentre 1:1 randomised controlled trial with two parallel groups (randomisation at the patient level, planned *N* = 1029, duration of study participation 12 months, implemented by 22 health care facilities nationwide). After 6 months, patients within the control group also receive the intervention. The primary outcomes are pain intensity and pain-related impairment, measured as Characteristic Pain Intensity (PI) and Disability Score (DS) (Von Korff) (baseline to 6 months follow-up). Secondary outcomes are the number of sick leave days, sickness allowance, treatment costs, psychological distress, health-related quality of life, catastrophising, and patient-related satisfaction with the intervention. The effects of the intervention will be analysed by a parallel-group comparison between the intervention and control groups. In addition, the long-term effects within the intervention group will be observed and a pre-post comparison of the control group before and after the intervention will be performed.

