**Fig. 1 Fig1:**
[figure not shown]
Timeline and analysis approach

Intervention effects will be analysed as follows:Essentially, the intervention effect will be evaluated by analysing the course of the primary and secondary outcomes in the intervention and control groups within the first 6 months (parallel-group comparison, *t*_0_ to *t*_2_) (Fig. 1b).In a secondary analysis approach, the long-term course of the new intervention is examined (*t*_2_ to *t*_4_). Further analyses of the outcome variables at these points are important for evaluating the stability of this effect over time (long-term) (Fig. 1c).The control group receives the intervention in the second half of the study period. The course of the primary and secondary outcomes in the control group after starting the intervention (*t*_0_ to *t*_2_ vs. *t*_2_ to *t*_4_) will be analysed (Fig. 1d). From a methodological perspective, this pre-post comparison can also help mitigating selection biases by increasing the willingness to participate in the study and reducing the drop-out rate within the control group.

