### Outcomes {12}

#### Primary outcomes

The primary outcomes are (1) characteristic pain intensity (PI) and (2) disability score (DS) for pain-related impairment. PI and DS are collected at baseline (*t*_0_) and at 3-, 6-, 9- and 12-month follow-up (*t*_1_ to *t*_4_). Changes in the primary outcomes between baseline (*t*_0_) and 6-month follow-up (*t*_2_) are evaluated as primary endpoints. Data are collected through a patient questionnaire, which includes the following:

(1) Characteristic pain intensity and (2) disability score are components of the Von Korff Chronic Pain Grade Scale (CPGS) [16]. The CPGS is a multidimensional measure with 7 items covering the two mentioned dimensions of overall chronic pain severity. The PI score is calculated as the average of three 0–10 ratings for ‘pain right now’, ‘average pain’ and ‘worst pain’, which is then multiplied by 10 to obtain a 0–100 score. The DS score is derived from the average of three 0–10 ratings for ‘daily activities’, ‘social activities’, and ‘work activities’, also multiplied by 10 to produce a 0–100 score. The last item covers the disability days.

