### Methods in analysis to handle protocol non-adherence and any statistical methods to handle missing data {20c}

In longitudinal analyses involving more than one follow-up time point, the family of (generalised) mixed models uses all available data, even if data at some time points are missing. If necessary (e.g. in case of high drop-out-rates > 30%), appropriate methods of (multiple) imputation of missing values will be employed. The population for primary analysis includes all patients for whom PI and DS data are available at baseline and at 6-months-follow-up.

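### The primary model's dependent variable carries the wrong visit code: t3 is month 9 in the protocol's own schedule, while the intended 6-month visit is t2

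*Protocol article*

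**What the plan says.** Section {20a} (Statistical methods for primary and secondary outcomes) specifies a linear mixed model with a random intercept for each of the two primary outcomes, characteristic pain intensity (PI) and disability score (DS). It describes the outcome first by month, as "pain intensity and disability score at 6 months adjusted for baseline values". The next sentence fixes the dependent variable by visit code and month together: "The values of the primary outcomes at time *t*_3_ (6-month follow-up) serve as the dependent variables".

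The visit schedule is set in the Primary outcomes section: "PI and DS are collected at baseline (*t*_0_) and at 3-, 6-, 9- and 12-month follow-up (*t*_1_ to *t*_4". The same section defines the endpoint: "Changes in the primary outcomes between baseline (*t*_0_) and 6-month follow-up (*t*_2_) are evaluated as primary endpoints". The analysis approach under Fig. 1 (Trial design {8}) gives the main between-arm analysis as "parallel-group comparison, *t*_0_ to *t*_2".

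On the control arm, the abstract states: "After 6 months, patients within the control group also receive the intervention". Trial design {8} describes this as an option that opens after six months of standard care.

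**The concern.** The sentence that defines the confirmatory dependent variable pairs a code with a month, and the pairing contradicts the protocol's own schedule. The code points to month 9 and the words point to month 6.

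The choice of visit matters in this design because control patients are offered A-IMPT after month 6. A between-arm comparison at month 6 sets the intervention against standard care. At month 9 it would set the intervention against a mixture of controls who have nearly finished the course, are still attending it, or have declined it. Both primary endpoints would be affected in the same way.

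Table 2 heads its columns with visit codes and not months, so selecting data by code is a realistic route to the wrong visit. The article was also published to restate the primary endpoints and the primary period after recruitment fell short, so this is a definition that readers will look up.

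**Working it through.** **Step 1. Map codes to months.** The schedule in Primary outcomes runs in three-month steps, so month = 3 × index:

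| Code | Month |
|---|---|
| t0 | 0 |
| t1 | 3 |
| t2 | 6 |
| t3 | 9 |
| t4 | 12 |

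The pairing of t3 with month 6 in {20a} does not reproduce. Month 6 is t2, and t3 is month 9.

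**Step 2. Set the statements about the primary time point side by side.**

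| Place | Code | Month in words |
|---|---|---|
| Abstract, Methods | none | 6 |
| Abstract, note on the protocol update | none | 6 |
| Objectives {7}, both hypotheses | none | 6 |
| Trial design {8}, text under Fig. 1 | t2 | 6 |
| Primary outcomes {12} | t2 | 6 |
| Sample size {14} | t2 | 6 |
| {20a}, sentence on the model | none | 6 |
| {20a}, sentence on the dependent variable | **t3** | 6 |
| {20c}, primary analysis population | none | 6 |

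Every entry gives month 6, and one code disagrees. The population rule in {20c} is telling: "The population for primary analysis includes all patients for whom PI and DS data are available at baseline and at 6-months-follow-up". A population defined by having 6-month data fits a 6-month outcome and would be out of place for a 9-month one.

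**Step 3. What is different at a true t3.** From month 6 to month 9 is 3 × 365.25 / 12 / 7 = 13.0 weeks. The intervention description {11a} spreads the ten sessions over 12 weeks. A control patient who started at once would be at or near the end of the course at t3. The text under Fig. 1 treats t2 to t4 as the period in which controls are followed after starting the intervention, so by the protocol's own layout t3 lies outside the randomised window.

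**Step 4. Can the dilution be sized?** It depends on c, the share of the treatment effect that the control arm as a whole has gained by month 9. The documents give no value for c, so it is an assumption throughout. For illustration, take the 0.3 SD difference, unit residual variance and 500 analysed patients from Sample size {14}, split 250 per arm. Take alpha 0.05 / 2 = 0.025 for two endpoints under Bonferroni, and no centre clustering. Then

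power ≈ Φ(0.3 × (1 − c) × √(250 / 2) − 2.241)

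| c (assumed) | Remaining difference (SD) | Power |
|---|---|---|
| 0 | 0.300 | 0.867 |
| 0.25 | 0.225 | 0.608 |
| 0.50 | 0.150 | 0.286 |
| 0.75 | 0.075 | 0.080 |
| 1 | 0 | 0.012 (one tail; 0.025 counting both) |

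The c = 0 row is not the protocol's 80%. That figure comes from a multilevel simulation whose clustering inputs the article does not give. The table spans almost the whole range of possible power, so it shows the direction of the harm and does not estimate its size. It applies only if month-9 data were used.

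**The case against.** The strongest reply is that this is a slip of one subscript and no reader would be misled. The sentence carries its own correction in parentheses, the sentence before it gives the month, and the endpoint definition, both hypotheses, the sample size section and the analysis population all agree on month 6. The text under Fig. 1 already confines the between-arm comparison to t0 to t2. Nothing in the article calls month 9 primary. All of this stands, and it settles what was intended.

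A reader might infer from the code alone that the primary analysis compares treated patients with treated patients, or that the confirmatory visit cannot be determined. The documents support neither reading. The first requires discarding the words next to the code. The second fails against the table in step 2. It would also be too strong to say that controls have already received the intervention at month 9: they have been offered it, some may decline, and the course nearly fills the interval, so some may still be attending.

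What the reply does not remove is the contradiction itself, which sits in the operative definition of the primary model. The same section still describes a Bonferroni adjustment for three outcome measures and two follow-up times, against the two endpoints and single time point stated elsewhere. The section was therefore not fully brought into line with the revision, which is a reason to correct the code and not leave it to the reader.

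**Conclusion.** The point holds as a labelling error. The code t3 in the definition of the primary dependent variable is wrong by the protocol's own schedule, and the intended visit is t2 at month 6. The primary comparison is sound once read by month.

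The consequence is conditional. If the code were followed literally, the randomised contrast would be diluted for both primary endpoints, because controls have by then been offered A-IMPT. The documents do not give the uptake, the starting times or the share of benefit gained by month 9, so the dilution cannot be quantified from them. The power figures in the working rest on an assumed share and on ignoring clustering, and should not be read as a loss of power in the plan. This is a small correction, to be made before the analysis is programmed.

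**What to change.** In section {20a}, change t3 to t2 in the sentence that defines the dependent variable, so that the confirmatory between-arm comparison uses t2 (6 months). This matches the text under Fig. 1, Primary outcomes {12}, Sample size {14} and the population in {20c}. If a safeguard is wanted, one clause can say that t2 is the only visit used for the confirmatory comparison; the text under Fig. 1 already implies this. If a separate statistical analysis plan or programming specification exists, check that it uses the same code.

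The cost is one character and, optionally, one clause. Sample size, alpha, power and data collection are unaffected.

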**Additional variables**							
***Control***	Therapy expectation	X					
***Process***	Physical activity	X	X	X	X		X
	Flexible self-regulation	X	X	X	X		X
	Health literacy	X	X	X	X		X

^1^Additional follow-up for control and process variables, 5th week of intervention

^2^Data is available 6–9 month after treatment delivery

During the course of the project, the number of primary outcomes was reduced from three to two. PI and DS are the primary outcomes, while satisfaction with intervention, previously also a primary outcome, is now considered a secondary outcome. This change was necessary to ensure that the main effects of the intervention could be analysed with sufficient power, given the number of cases available.

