### Sample size {14}

During the initial phase of the project, it became clear that the originally planned sample size could not be achieved. For this reason, the required number of cases was recalculated based on the assumption that only two primary endpoints, including characteristic pain intensity (PI) and disability score (DS), would be investigated and that the primary analysis would refer to the 6-month measurement time point.

To determine the required number of cases, a simplified multilevel model was employed to examine group differences between standardised mean differences (SRMs) for the two primary outcome measures in the primary analysis approach. The SRM is calculated by dividing the pre-post differences between baseline and follow-up values (t0 to t2) by the respective standard deviation of the pre-post differences. The group differences are statistically tested using regression analyses, with the SRMs as the dependent variable and the group membership as the predictor variable.

Power calculation was performed using MLPowSim [33] in a simulation of power to detect group differences. The effect size was defined as the difference between group-specific SRMs, accounting for a residual variance of 1.0. The differences between the SRMs can therefore be interpreted directly as effect sizes. A value of 0.3 was chosen as the group difference to be detected. This corresponds to the size of a minimally significant difference in numerical rating scales in pain research [34]. Type I and type II errors were set at α = 0.05 and β = 0.20, respectively.

The results of the sample size calculation indicated a final sample size of 500 cases (statistical power of 80%, 2-sided significance level of 0.05). An expected drop-out of 20% over the 6-month comparison period leads to an increase in the required number of cases to be randomised initially to *N* = 782. Therefore, it is estimated that approximately *N* = 1029 individuals need to be screened to assess their eligibility criteria.

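### Holm in place of single-step Bonferroni for PI and DS at 6 months would keep the same familywise error and raise the chance of confirming both hypotheses

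*Protocol article*

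**What the plan says.** The Protocol article, Statistical methods {20a}, analyses PI and DS at 6 months, each adjusted for its baseline value, and then fixes the multiplicity rule: "As two primary endpoints are analysed simultaneously, adjustment for multiple testing using Bonferron’s method will be applied". The general significance level in the same section is two-sided 0.05.

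The last paragraph of that section gives a second rule for the confirmatory analysis: "a Bonferroni adjustment for multiple testing (3 outcome measures, 2 follow-up times) is applied". This does not fit the current design of two endpoints at one time point.

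Sample size {14} works with "statistical power of 80%, 2-sided significance level of 0.05" and mentions no split of alpha. Objectives {7} lists two separate working hypotheses, one for pain intensity and one for disability. The text below Table 2 explains why the number of primary outcomes was cut from three to two: "This change was necessary to ensure that the main effects of the intervention could be analysed with sufficient power, given the number of cases available".

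**The concern.** The trial was redesigned because recruitment fell short, and power is the stated reason for dropping a primary endpoint. Single-step Bonferroni then tests PI and DS at 0.025 each, even when the other endpoint is already clearly significant. Holm compares the smaller p-value with 0.025 and, only if that is significant, the larger one with 0.05. It needs no further data, model or assumption about how PI and DS are related.

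At stake is the second hypothesis. If one endpoint succeeds and the other has a p-value between 0.025 and 0.05, Bonferroni leaves the second unconfirmed where Holm would confirm it at the same familywise error.

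**Working it through.** **Inputs from the Protocol article.** Effect size: "A value of 0.3 was chosen as the group difference to be detected" (Sample size {14}). Variance: "accounting for a residual variance of 1.0" (same section), so SD 1. Allocation: "allocated to either the intervention group or the control group in a 1:1 ratio" (Trial design {8}). Analysable patients: 500, or 250 per arm (Sample size {14}). Two-sided alpha 0.05.

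**Assumed.** The correlation ρ between the two test statistics. None is given. PI and DS come from the same scale, so a positive value is plausible; 0.3 to 0.8 is shown. Both endpoints are taken to have the same true effect.

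**The plan's own figure first.** For independent observations, n per arm = 2(z₁₋α/₂ + z₀.₈)²/0.3².
- α = 0.05: 2(1.960 + 0.842)²/0.09 = 174.4, so 175 per arm, 350 in total.
- α = 0.025: 2(2.241 + 0.842)²/0.09 = 211.2, so 212 per arm, 424 in total.

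Neither gives 500. The article used a multilevel simulation and does not state the centre variance, so 500 is not shown to be wrong. It would imply a design effect of 500/350 = 1.43 at 0.05, or 500/424 = 1.18 at 0.025. Two scenarios are therefore shown:
- **A:** each endpoint has exactly 80% power at unadjusted 0.05, as Sample size {14} states. Expected test statistic 1.960 + 0.842 = 2.802.
- **B:** 500 independent patients. Expected test statistic 0.3 × √(250/2) = 3.354.

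**Formulas.** Let Z₁ and Z₂ be bivariate normal with that mean and correlation ρ (the opposite tail is negligible).
- Bonferroni, per endpoint: P(Z₁ > 2.241). Both: P(Z₁ > 2.241 and Z₂ > 2.241).
- Holm adds, per endpoint, g = P(1.960 < Z₁ ≤ 2.241 and Z₂ > 2.241), and for both endpoints 2g.
- At least one endpoint: the same event under both methods, so the same power.

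**Results (Bonferroni → Holm).**

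| Scenario | ρ | Per endpoint | Both | At least one |
|---|---|---|---|---|
| A | 0.3 | 71.2% → 76.9% | 54.4% → 65.7% | 88.0%, unchanged |
| A | 0.6 | 71.2% → 76.2% | 58.8% → 68.8% | 83.7%, unchanged |
| A | 0.8 | 71.2% → 75.6% | 62.5% → 71.3% | 79.9%, unchanged |
| B | 0.3 | 86.7% → 90.7% | 76.8% → 84.8% | 96.6%, unchanged |
| B | 0.6 | 86.7% → 90.2% | 79.1% → 86.1% | 94.3%, unchanged |
| B | 0.8 | 86.7% → 89.7% | 81.3% → 87.2% | 92.1%, unchanged |

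**Familywise error.** In simulation with no effect on either endpoint, both methods give 0.0495, 0.0467 and 0.0431 at ρ = 0, 0.5 and 0.7.

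**In patients.** With independent observations, 80% power per endpoint takes 424 under Bonferroni and about 372 to 384 under Holm (ρ from 0 to 0.7), a difference of 40 to 52.

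**The second Bonferroni sentence.** Read as 3 × 2 = 6 tests, it gives 0.05/6 = 0.0083 per test. In scenario B, power per endpoint is then 76.3% instead of 86.7%, a loss of about 10 points. That is more than the choice between Bonferroni and Holm costs.

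**The case against.** Bonferroni for two co-equal endpoints is valid, prespecified and conservative, so on this view the point is a preference. That stands as far as it goes: nothing in the first multiplicity sentence is wrong, and the point is one of efficiency only.

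A reader might infer that Holm is more powerful for every purpose. It is not. The article does not say whether success needs one endpoint or both, and if one suffices, Holm gains nothing on that criterion. The gain does count for two separately stated hypotheses.

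A reader might also infer that Bonferroni leaves the trial short of its 80% target. The article does not support that. The 71% in scenario A rests on taking 80% at unadjusted 0.05 literally. With 500 independent patients the figure is 86.7%, and because the centre variance is not stated, neither scenario can be called the right one.

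Nor does the argument depend on PI and DS being positively related. Holm is valid under any dependence, and its gain shrinks as the correlation rises.

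Two costs are real. A second-step Holm rejection can go with a 97.5% interval that includes zero, so keeping decisions and intervals aligned is a legitimate reason to stay with Bonferroni. And recruitment ended on 28/02/2024, the trial is not blinded, and the primary endpoints have already been changed once for power. A further change that favours rejection is credible only if it is made before outcomes are seen by arm, and the article does not say whether they have been.

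**Conclusion.** The point holds as a low-cost improvement. Holm keeps the two-sided familywise error at 0.05, never rejects less than the planned procedure, and leaves power for at least one endpoint unchanged. For correlations of 0.3 to 0.8, it adds about 4 to 6 points per endpoint and 9 to 11 for both if each endpoint has 80% power at unadjusted 0.05, or about 3 to 4 and 6 to 8 points with 500 independent patients. These sizes rest on the assumed correlations and on equal effects for the two endpoints; that Holm never rejects less rests on neither. The change cannot be applied cleanly while the section also carries the sentence on three outcomes and two follow-up times.

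**What to change.** Replace both multiplicity statements in Statistical methods {20a} with one rule: PI and DS at 6 months are tested by the Holm procedure at a two-sided familywise alpha of 0.05, the smaller p-value against 0.025 and, if it is significant, the larger against 0.05. Delete the reference to three outcome measures and two follow-up times. State that any 97.5% simultaneous intervals are supplementary to the Holm decision and may not match a second-step rejection. Date the change, and record that no comparison of outcomes by arm had been made. If such a comparison has already been made, keep Bonferroni for the two endpoints and correct only the outdated sentence.

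The cost is a short edit to one section. Patients, data collection and the analysis model do not change.
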